## **10. TRIAL DESIGN**

### **10.1 Description**

This is a randomized, ivermectin-controlled, double-blind, single-ascending-dose, parallel design, inpatient/outpatient study of moxidectin administered to subjects of both sexes with different degrees of severity of *O. volvulus* infection. A total of 192 subjects will be enrolled in consecutive cohorts and will receive a single oral dose of moxidectin or a standard dose of ivermectin. Moxidectin is available in 2 mg TIC (tablets in capsules). Three (3) dose levels of moxidectin will be studied: 2 mg, 4 mg, and 8 mg. Therefore, the dose of moxidectin will be either 1 TIC for the 2mg, 2 TIC for the 4 mg, or 4 TIC for the 8 mg dose group.

Ivermectin will be dosed according to the approved weight based dosing schedule (see section 17.1).

To ensure blinding, moxidectin-treated and ivermectin-treated subjects may receive a number of placebo capsules so that each subject receives 4 capsules. All doses will be given after an overnight fast and breakfast will be delayed for about 2 hours.

Enrollment will be by dose and severity of infection as indicated below. The intensity of infection will be based on the mean of the densities at the iliac crests and calves. At each dose level, subjects with  $> 0$  and  $< 10$  microfilariae/mg of skin must have no ocular involvement. The sum of microfilariae in the two eyes must be  $\leq 10$  in subjects with 10-20 microfilariae/mg of skin.

- Cohort 1: 2 mg, 16 subjects with  $> 0$  and  $< 10$  microfilariae/mg of skin

- Cohort 2: 2 mg, 16 subjects with 10-20 microfilariae/mg of skin and the sum of microfilariae in the two eyes must be  $\leq 10$
- Cohort 3: 2 mg, 32 subjects with  $> 20$  microfilariae/mg of skin with or without ocular involvement (this cohort will be enrolled in two groups of 16 subjects due to the capacity of the site)
- Cohort 4: 4 mg, 16 subjects with  $> 0$  and  $< 10$  microfilariae/mg of skin
- Cohort 5: 4 mg, 16 subjects mg, with 10-20 microfilariae/mg of skin and the sum of microfilariae in the two eyes must be  $\leq 10$
- Cohort 6: 4 mg, 32 subjects with  $> 20$  microfilariae/mg of skin with or without ocular involvement (this cohort will be enrolled in two groups of 16 subjects due to the capacity of the site)
- Cohort 7: 8 mg, 16 subjects with  $> 0$  and  $< 10$  microfilariae/mg of skin
- Cohort 8: 8 mg, 16 subjects with 10-20 microfilariae/mg of skin and the sum of microfilariae in the two eyes must be  $\leq 10$
- Cohort 9: 8 mg, 32 subjects with  $> 20$  microfilariae/mg of skin with or without ocular involvement (this cohort will be enrolled in two groups of 16 subjects due to the capacity of the site)

The decision to move to the next cohort within one dose group will be made by the PI based on evaluation of all blinded data obtained during the first 30 days post treatment of the previously enrolled cohort(s). The PI will inform the sponsors of this decision prior to enrollment of the next cohort. If either of the sponsors disagrees, cohort progression will be put on hold until the disagreement is resolved.

The decision to move to the next higher dose group, will be made based on blinded review of the safety and microfilaricidal data obtained during the first 30 days post treatment of all previously enrolled cohorts. The PI will submit a recommendation to proceed or not to proceed after a detailed examination of the blinded data. The Wyeth Medical Monitor, the WHO Clinical Monitor and the WHO Project Manager will conduct their separate review of the blinded data. Wyeth will include a representative of its safety surveillance group in addition to the medical monitor for purposes of review. WHO may include its Clinical Coordinator in the review.

The Project Review Team (PRT), consisting of Wyeth and WHO/TDR reviewers and the PI, will discuss the blinded data and formulate a recommendation to progress or not. The recommendation will be provided together with the rationale for this recommendation to the Clinical Expert Review Team (CERT)

consisting of three clinical experts (not otherwise associated with the conduct of the study) who have access to the randomized dose assignments in patient envelopes and have reviewed the data in parallel with the PRT. The CERT will initially review the data in a blinded fashion. They can make their recommendation on dose progression based on blinded data. If they need to unblind, they may do so for individual patient(s), or they may unblind the entire cohort. In either case, they will inform the PRT of their recommendation on dose progression without disclosing if the decision was made on blinded or unblinded data. If there is a difference of opinion within the PRT regarding the dose progression recommendation, the different recommendations and their rationale will be provided to the CERT. The CERT will provide their recommendation to PRT. If there is not unanimous agreement among the CERT, they will provide their differing recommendations and their rationale. If there is not unanimous agreement on proceeding to the next dosing cohort between the PRT, and a majority of the CERT, the data will be discussed in a blinded fashion. If no agreement can be reached, unblinded data will be made available to the PRT and discussed. If upon discussion of the unblinded data there is no unanimous agreement to proceed to the next higher dose group, dose progression will not occur.

The diagram below provides an overview of the process from enrollment of the first cohort (2 mg) to decision to progress to the 4 mg dose as well as treatment and study participation for each subject. The same process will be followed for the cohorts in the 4 mg dose group and the decision to move to the 8 mg dose.

### Enrollment Process and Dose Progression Decision Diagram

[figure not shown]

A schematic presentation of procedures is provided in the subject flowchart (section 9).

## 11. STUDY OBJECTIVES

### 11.1 Primary

The primary objective of this study is to determine the safety and tolerability of orally administered moxidectin in subjects with *O. volvulus* infection, as measured by the incidence of clinical AEs and clinically significant laboratory test results.

### 11.2 Secondary

The secondary objectives of this study are:

1. To determine doses that effectively eliminate microfilariae and prevent their reaccumulation in the skin as measured by the skin microfilarial loads at day 8, 1 month, 2 months, 3 months, 6 months, 12 months and 18 months after treatment.
2. To determine the viability and fertility of adult worms at 18 months.
3. To assess the pharmacokinetics of moxidectin in adult male and female subjects.

## **12. SELECTION OF STUDY POPULATION**

This study will be conducted in otherwise healthy subjects with *O. volvulus* infection from the OCRC study area in the basin of River Tordzi, located in the forest area of south-eastern Ghana and within a 2 to 2½ hours journey from Hohoe, the location of the study site. The Onchocerciasis Control Programme (OCP) had established in 1988, during the southern extension of the program, that transmission of onchocerciasis in the area involved forest vectors exclusively and hence no control activities were instituted. The area was also not included in the ivermectin distribution program launched by the Directorate for Onchocerciasis Control of the Ministry of Health, as the area is largely hypoendemic for onchocerciasis. Extensive clinical, ophthalmologic and parasitological surveys carried out by the OCRC showed that morbidity due to onchocerciasis was low. The vast majority of adults had no skin or ocular lesions. Where ocular lesions were found they were mainly non-onchocercal. This was in line with the observation during initial contact with the area that most villages had never heard of onchocerciasis, the *Simulium* fly, or of ivermectin and very few had attended any health institution for skin or ocular problems or for the excision of nodules. Thus the OCRC only offered individualized treatment with ivermectin to those found during surveys to have clinically significant onchocercal lesions. The communities were informed of the existence elsewhere of mass treatment with ivermectin and the availability of the drug at nearby centers.

Subjects will be members of a “grand cohort” who were previously prescreened in their villages and the hospital and who have been dormant, pending further testing and enrollment in the appropriate clinical trial.

The ‘grand cohort’ was identified previously in a step-wise process consisting of (1) identification of potentially suitable villages based on entomological data collected by the Onchocerciasis Control Programme, and/or indirectly via OCRC out-patients with high skin microfilaria counts from these villages, and/or known breeding sites of *Simulium* close to these village and/or village residents reporting a high prevalence of onchocerciasis and *Simulium* bite rates, (2) an initial meeting with the village chief, elders and opinion leaders during which the information provided in a ‘generic information sheet’ (e.g.

background on onchocerciasis, purpose of the OCRC, purpose and procedures for screening, general purpose and procedures for three types of studies (clinical drug efficacy and safety study, ‘ex vivo’ study of the efficacy of drugs on the macrofilariae, PK study) is presented and discussed, (3) a meeting with the community in which the same information was presented and discussed, after the village chief, elders and opinion leaders had provided their agreement to such a meeting, (4) a village survey, after the community had agreed to that, (5) a screen at Onchocerciasis Chemotherapy Research Centre in the Government Hospital at Hohoe for those subjects that, based on the village survey, had *O. volvulus* infection, were 18-60 years old, had no obvious exclusion factors, and had agreed to the hospital screen. The results of the screening were communicated to the subjects. Subjects who could potentially qualify for a clinical trial form the ‘grand cohort’ from which subjects for future studies will be recruited. Informed consent was obtained at all stages of contact with the communities listed above. The “generic” informed consent form was the basis for the transfer of information and the subsequent discussions. The consent prior to the hospital-screening phase was verbal and involved thousands of people in the initial stages and a few hundred in the hospital-screening phase.

For recruitment for this study, subjects on the ‘grand cohort’ list will be asked to come for screening per cohort, based on position of their name on the list, gender and microfilaria counts. If a subject asked to come for screening for a particular cohort meets all inclusion criteria and has none of the exclusion criteria, but has a microfilaria count too high or too low for that cohort, they will be offered the choice between (1) enrollment into the next cohort for which they qualify based on their microfilaria count or (2) nodulectomy and ivermectin treatment. If their microfilaria count is too low or too high for any cohort planned in the future, they will be offered nodulectomy and ivermectin treatment. The same will happen, if they do not meet one of the other inclusion criteria or meet an exclusion criterion (see figure below) or if 16 subjects higher on the grand cohort list have already qualified for the study.

All members of the grand cohort who are invited for this study participate in a written and signed or thumb printed informed consent process. During this process, the PI or sub-investigator informs the subjects of all the elements specific to the study. An information sheet that is specific to the study and is available in English and the local language replaces the generic information sheet. Adequate time is then allowed, as during the earlier discussion, for the subject to ask questions and make a voluntary decision. No protocol-specific procedures, including transport to the study site and screening, will be performed until the subject has signed or thumb printed and dated an ethics committee (EC) approved informed consent form. The form will be witnessed by a member of the community (impartial witness) and

countersigned by the investigator. A copy will be given to the subject. The study begins at the time the first subject is admitted to the hospital for the study. Subjects must meet all the inclusion and none of the exclusion criteria to be enrolled in the study.

OCRC informs each subject individually about the details of the study, which concern him/her from the time of enrollment to completion. This includes AEs, lab results etc. and the final status. If there are any outstanding medical issues, further advice is given.

Following completion of the study, the PI and his staff will seek an appointment with the chiefs and the elders and discuss the overall findings and conclusions of the study with them. Subsequently, study results and conclusions are presented and discussed at a village durbar. The discussions with chiefs and elders as well as those at the village durbar include the implications of the study results for future studies on moxidectin as well as other research.

### Consent Process Diagram

[figure not shown]

## **12.1 Inclusion Criteria**

Men and women in good general health, with *O. volvulus* infection and:

- a) Written, signed (or thumb-printed), and dated informed consent
- b) Aged 18 to 60 years, inclusive
- c) Body weight  $\geq 40$  kg for women and  $\geq 45$  kg for men
- d) Nonpregnant, nonbreastfeeding women. Women of child-bearing potential must agree to use birth control during the first 150 days after treatment.
- e) Healthy, as determined by a physician on the basis of a physical examination, ECG, and a thorough review of the medical history and clinical laboratory results
- f) Adequate hematologic, renal, and hepatic function, defined as:
  - 1) White blood cell (WBC) count  $\geq 2,800$  and  $\leq 11,300$  cells/mL
  - 2) Hemoglobin:  $\geq 11.0$  g/dL for men and  $\geq 10.0$  g/dL for women
  - 3) Platelet count:  $\geq 110,000$  mm^3
  - 4) Serum creatinine:  $\leq 1.25$  x upper limit of normal (ULN)
  - 5) Total bilirubin:  $\leq 1.25$  x ULN
  - 6) AST/SGOT:  $\leq 1.25$  x ULN
  - 7) AP:  $\leq 1.25$  x ULN
  - 8) Prothrombin time WNL
  - 9) Urinalysis WNL
- g) Skin microfilarial density within the required range for the cohort

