| Diagnosis and Main Criteria for Inclusion | 
Men and women in good general health, with O. volvulus infection and:
 
 
a) Written, signed (or thumb-printed), and dated informed consent
 
b) Aged 18 to 60 years, inclusive
 
c) Body weight <math>\geq 40</math> kg for women and <math>\geq 45</math> kg for men
 
d) Nonpregnant, nonbreastfeeding women. Women of child bearing potential must agree to use birth control during the first 150 days after treatment.
 
e) Healthy, as determined by a physician on the basis of a physical examination, ECG, and a thorough review of the medical history and clinical laboratory results
 
f) Adequate hematologic, renal, and hepatic function, defined as: 
 
1) White blood cell (WBC) count <math>\geq 2,800</math> and <math>\leq 11,300</math> cells/mL
 
2) Hemoglobin: <math>\geq 11.0</math> g/dL for men and <math>\geq 10.0</math> g/dL for women
 
3) Platelet count: <math>\geq 110,000</math> mm^3
 
4) Serum creatinine: <math>\leq 1.25</math> x upper limit of normal (ULN)
 
5) Total bilirubin: <math>\leq 1.25</math> x ULN
 
6) AST/SGOT: <math>\leq 1.25</math> x ULN
 
7) AP: <math>\leq 1.25</math> x ULN
 
8) Prothrombin time WNL
 
9) Urinalysis WNL
 
 
 
g) Skin microfilarial density within the required range for the cohort
 
 |

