| Hemoglobin (Hgb)                                                                                                                       | WNL    | 10-<25% reduction                                                                                  | 25-<50% reduction                                                                 | 50-<75% reduction                                                   | ≥75%                                                                                                           |
| Leukocytes (total WBC)                                                                                                                 | WNL    | < LLN - $2.5 \times 10^9$ /L                                                                       | $1.5 - < 2.5 \times 10^9$ /L                                                      | $1.0 - < 1.5 \times 10^9$ /L                                        | $< 1.0 \times 10^9$ /L                                                                                         |
|                                                                                                                                        | WNL    | > $11.3 - 19.0 \times 10^9$ /L                                                                     | > $19.0 - 38.0 \times 10^9$ /L                                                    | > $38.0 - 57.0 \times 10^9$ /L                                      | > $57.0 \times 10^9$ /L                                                                                        |
| Note: Contributory factors include Mazotti reaction (leucocytosis), coincidental infection (exclude) drug effect                       |        |                                                                                                    |                                                                                   |                                                                     |                                                                                                                |

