| Neutrophils/granulocytes (ANC/AGC)                                                                                                     | WNL    | ≥1500 - <2000/mm                                                                       | ≥1000 - <1500/mm                                                      | ≥500 - <1000/mm                                         | < 500/mm                                                                                           |
|                                                                                                                                        | WNL    | >6080-12160/mm                                                                         | >12160-24320/mm                                                       | >24320-36480/mm                                         | >36480/mm                                                                                          |
| Note: Contributory factors include Mazotti reaction (neutrophilia), coincidental infection (exclude) drug effect                       |        |                                                                                                    |                                                                                   |                                                                     |                                                                                                                |
| Lymphocytes                                                                                                                            | WNL    | <LLN - 1000/mm                                                                         | ≥500 - <1000/mm                                                       | <500/mm                                                 | -                                                                                                              |

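### The white-cell entry limits are printed per mL, a unit slip that puts a binding eligibility threshold a factor of 1,000 below the protocol's own WBC scale

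*Supplement*

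**What the plan says.** In the latest protocol version, section 12.1, criterion f.1 reads "White blood cell (WBC) count $\geq 2,800$ and $\leq 11,300$ cells/mL". The synopsis carries the same limits in the same unit. The criterion is one of a list that defines adequate blood, kidney and liver function. Criterion e), just above it, asks a physician to judge the subject healthy, with the laboratory results among the grounds. Section 12 makes the list binding: "Subjects must meet all the inclusion and none of the exclusion criteria to be enrolled in the study". Section 12.4 defines anyone who consents and does not meet the criteria as a screen failure.

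Attachment 5 (the OCRC toxicity criteria, haematological part) grades total leukocytes in units of 10^9/L. Its first grade of leukocytosis is "> $11.3 - 19.0 \times 10^9$ /L", and its grade 4 leukopenia is any value below 1.0 × 10^9/L. White-cell subsets in the same table are given per mm3; grade 1 neutropenia, for example, is "≥1500 - <2000/mm 3".

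The platelet criterion two lines below f.1 reads "Platelet count: $\geq 110,000$ mm 3", with no slash or 'per' before the unit.

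**The concern.** The entry limit and the safety grading concern the same measurement in the same subjects, and the figures 11,300 and 11.3 plainly refer to the same boundary. They agree only if the entry limit is counted per mm3, and the protocol prints per mL. An eligibility limit decides who enters the trial, unlike background text. As printed, it would have to be silently reinterpreted each time it is applied, and a strict reading turns away every subject with a normal white count.

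**Working it through.** **Inputs**

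- Entry window: 2,800 to 11,300 cells/mL (section 12.1 f.1 and synopsis).
- Grade 4 leukopenia: below 1.0 × 10^9/L (Attachment 5).
- Start of leukocytosis grade 1: above 11.3 × 10^9/L (Attachment 5).
- Grade 1 leukopenia: from the lower limit of normal down to 2.5 × 10^9/L, with no number given for the lower limit of normal (Attachment 5).

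**Step 1: convert the printed limits.** 1 L = 1,000 mL, so cells/L = cells/mL × 1,000.

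- Lower: 2,800 × 1,000 = 2,800,000 cells/L = 0.0028 × 10^9/L (2.8 cells/mm3).
- Upper: 11,300 × 1,000 = 11,300,000 cells/L = 0.0113 × 10^9/L (11.3 cells/mm3).

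**Step 2: compare with grade 4.** The cut-off of 1.0 × 10^9/L is 1,000,000 cells/mL.

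- 1,000,000 / 11,300 = 88, so the upper entry limit is about 88 times below the cut-off.
- 1,000,000 / 2,800 = 357, so the lower entry limit is about 357 times below it.

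The whole printed window falls inside grade 4.

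**Step 3: compare with the leukocytosis boundary.** 11.3 / 0.0113 = 1,000 exactly. Identical digits and a whole power of ten point to a unit slip and not to a different intended limit.

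**Step 4: try the other unit.** Read per mm3 (1 mm3 = 1 µL, and 1 L = 1,000,000 mm3):

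- 2,800 × 1,000,000 = 2.8 × 10^9/L.
- 11,300 × 1,000,000 = 11.3 × 10^9/L.

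The upper limit now meets the Attachment 5 boundary exactly. The lower limit lies above the 2.5 × 10^9/L floor of grade 1 leukopenia, which is compatible. It is not independent confirmation, because 2.8 appears nowhere in the attachment.

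**Step 5: is this a reading error from the PDF?** A lost µ sign is conceivable. But the unit reads mL in both the synopsis and the criteria section of both protocol versions in the supplement, four places in all, while the µ sign survives elsewhere, for example in the µg/kg doses in section 16.1. A reading error is unlikely. The original page would settle it.

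**The case against.** The strongest reply is that nobody would be misled. The numbers are recognisable only as counts per mm3, the criterion stands beside a requirement that the subject be healthy, and Attachment 5 shows the right scale. A plausible but wrong limit would be more dangerous than one that is visibly impossible. This stands as to consequence: wrong enrolment or wrong exclusion is unlikely. It does not make the printed criterion correct, and no other place in the protocol restates the entry limit in a workable unit.

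A reader might also infer more than the documents support:

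- **That only subjects with grade 4 leukopenia could enrol.** Criterion e) closes that route, because a subject with about 11 white cells per mm3 would not be judged healthy. The literal result is that no one is eligible.
- **That monitors and range checks would flag all 192 subjects.** Section 24 plans automated checks for selected protocol violations and out-of-range data, but does not say that they are coded from the text of f.1. Section 25.2 requires the laboratory's normal values and units of measure, which are a likelier basis for range checks.
- **That Attachment 5 confirms both limits.** It confirms only the upper one.
- **That the platelet line is a fault of the same weight.** It lacks a 'per', which is clerical. Attachment 5 gives platelets per mm3, so the scale is not in doubt.

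**Conclusion.** The point holds as a unit error in a mandatory entry criterion. The printed limits are too low by a factor of exactly 1,000 against the protocol's own leukocytosis boundary, and the window as printed sits wholly within Attachment 5 grade 4. Read literally together with criterion e), it admits no one.

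The practical effect is probably small. Site staff would very probably apply the limit per mm3, Attachment 5 already grades white counts on a workable scale, and sample size, power, endpoints and analysis do not depend on this figure. The conclusion assumes that the extracted text shows the printed unit faithfully, which four consistent occurrences support. It also takes the 11.3 × 10^9/L boundary in Attachment 5 as evidence of the intended scale.

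**What to change.** In section 12.1 f.1 and in the synopsis, reconcile the unit with the Attachment 5 scale: cells/mm3, equivalently 2.8 to 11.3 × 10^9/L. Leave the numbers 2,800 and 11,300 as they are. Because Attachment 5 corroborates only the upper bound, the sponsor should confirm the lower bound against its source when making the change. Add 'per' (or a slash) before mm3 in the platelet criterion in the same edit.

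The cost is a text correction in two places, which can go into the next amendment. No procedure, visit or analysis changes.
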